# The efficacy of continuous-flow cryo and cyclic compression therapy after hip fracture surgery on postoperative pain: design of a prospective, open-label, parallel, multicenter, randomized controlled, clinical trial

**DOI:** 10.1186/s12891-016-1000-4

**Published:** 2016-04-08

**Keywords:** Hip fracture, Cryotherapy, Induced hypothermia, Intermittent pneumatic compression device, Pain, Analgesia, Opioid analgesics, Morphine, Hemoglobin, Delirium, Length of stay, Functional outcome, Patient-reported outcome, Complications

## Abstract

**Background:**

The number of hip fractures and resulting post-surgical outcome are a major public health concern and the incidence is expected to increase significantly. The acute recovery phase after hip fracture surgery in elder patients is often complicated by severe pain, high morphine consumption, perioperative blood loss with subsequent transfusion and delirium. Postoperative continuous-flow cryocompression therapy is suggested to minimize these complications and to attenuate the inflammatory reaction that the traumatic fracture and subsequent surgical trauma encompass. Based on a pilot study in patients undergoing total hip arthroplasty for osteoarthritis, it is anticipated that patients treated with continuous-flow cryocompression therapy will have less pain, less morphine consumption and lower decrease of postoperative hemoglobin levels. These factors are associated with a shorter hospital stay and better long-term (functional) outcome.

**Methods/design:**

One hundred and sixty patients with an intra or extracapsular hip fracture scheduled for internal fixation (intramedullary hip nail, dynamic hip screw or cannulated screws) or prosthesis surgery (total hip or hemiarthroplasty) will be included in this prospective, open-label, parallel, multicenter, randomized controlled, clinical superiority trial. Patients will be allocated to two treatment arms: group ‘A’ will be treated with continuous-flow cryocompression therapy and compared to group ‘B’ that will receive standard care. Routine use of drains and/or compressive bandages is allowed in both groups. The primary objective of this study is to compare acute pain the first 72 h postoperative, measured with numeric rating scale for pain. Secondary objectives are: (non-) morphine analgesic use; adjusted postoperative hemoglobin level; transfusion incidence; incidence, duration and severity of delirium and use of psychotropic medication; length of stay; location and duration of rehabilitation; functional outcome; short-term patient-reported health outcome; general and cryotherapy related complications and feasibility.

**Discussion:**

This is the first randomized controlled trial that will assess the analgesic efficiacy of continuous-flow cryocompression therapy in the acute recovery phase after hip fracture surgery.

**Trial registration:**

www.trialregister.nl, NTR4152 (23^rd^ of August 2013)

## Background

Hip fractures are one of the most important causes of long-term disability and a significant public health issue [1]. Incidence varies on a global scale [2, 3] but incidence is estimated to vary between 414 and 957 per 100,000 inhabitants in the USA [4]. Due to aging of the population in general a significant increase in hip fracture numbers is expected [5].

Hip fractures are a serious condition associated with high morbidity, one-year mortality rates up to 29 % [2, 4], severe pain [6, 7] and significant decline in functional status [8–11]. Less than 50 % of (semi-) independent living elders return to their pre-fracture habitat [11, 12]. Among the most serious of complications is the onset of delirium, which has a particular high incidence of 45 % in hip fracture populations [13–15]. Possibly because this condition is known to be extremely painful [15–18] and patients with pain are nine times more likely to develop a delirium [18–20] and furthermore take longer to ambulate and consequently, have longer length of stay [9].

Upon admission 40 % of hip fracture patients is anemic [21] and observed intraoperative blood loss is systematically underestimated; up to six-fold in excess in extracapsular fractures [22]. The continued postoperative decline in hemoglobin levels results from, among others, surgical site bleeding [22]. This yields a specifically high transfusion rate in this frail elderly patient category where use anticoagulants or thrombocyte aggregation inhibitors is relatively prevalent [23]. Besides (postoperative) surgical site bleeding, the fracture trauma and subsequent surgical stabilization procedure induce a inflammatory response causing leakage of plasma proteins and migration of inflammatory cells that lead to local peripheral vasodilatation and increased capillary permeability, ultimately causing edema [24]. Edema gradually develops during the first week post surgery, is more pronounced in intertrochanteric fractures and correlates well with reduced knee extension strength and functional performance [25, 26]. In an attempt to reduce edema and postoperative hemorrhaging compressive wound dressings are applied [27–29]. Dynamic pneumatic compressive devices not only reduce blood loss, edema and offer a better (hemo) dynamic profile in the deep venous and lymph system, it also exerts analgesic effects and reduces the inflammatory response when combined with a cryotherapy adjunct [30–35].

In a pilot study on 30 patients in a Dutch teaching hospital an apparatus with continuous-flow cryotherapy combined with intermittent compression was used in the postoperative setting of hip arthroplasty for end-stage osteoarthritis [36]. A trend towards lower visual analogue scale (VAS) pain scores and less morphine use was observed, and patients receiving continuous-flow cryocompression (CFC) therapy had statistical significant less decline in postoperative hemoglobin levels. In two randomized controlled trials evaluating continuous-flow cryotherapy (without a compression adjunct) in 45 total hip [37] and 208 total hip and knee arthroplasty [38] patients, lower pain scores were observed and less morphine was used. Furthermore length of stay was 1.4 days shorter when continuous-flow cryotherapy was applied after hip arthroplasty in 74 patients [39].

Currently all published trials studying CFC therapy focus on semi-elective procedures such as anterior cruciate ligament reconstruction and total knee arthroplasties [40]. To our knowledge, no randomized controlled trial exists evaluating the efficacy of CFC therapy in the acute postoperative recovery phase of hip fracture patients [40]. As hip fracture patients have duplicate trauma, severe pain, fracture site bleeding with related inflammation and associated soft tissue damage they are expected to benefit most from CFC therapy.

### Aim

The aim of the current study is to evaluate the efficacy of CFC therapy on pain in the first 72 postoperative hours of hip fracture patients. The secondary aim is to evaluate the effects on (non-) morphine analgesic use; postoperative hemoglobin level; transfusion incidence; delirium incidence and severity; use of psychotropic medication; length of stay; short-term location and duration of rehabilitation; functional outcome; short-term patient-reported health outcome; general and cryotherapy related complications. Furthermore the feasibility of a cryocompression device on orthopedic/surgery wards is assessed.

We hypothesized that: 1) CFC therapy will lower perceived pain levels and morphine consumption; and 2) will reduce postoperative blood loss and transfusion incidence; and 3) reduced pain by CFC therapy will lead to lower delirium incidence and 4) enhance functional recovery, leading to shorter length of stay in postoperative hip facture patients.

## Methods

### Study design

This study is designed as a prospective, open-label, parallel, multicenter, 1:1 randomized controlled, clinical superiority trial in accordance with CONSORT and SPIRIT guidelines [41, 42]. Eight orthopedic, surgery and/or geriatric departments of three middle sized teaching hospitals and one academic hospital in the Netherlands will participate: The Spaarne Gasthuis, Hoofddorp and Haarlem; Noordwest Ziekenhuisgroep, Alkmaar; Amstelland Hospital, Amstelveen; VU University Medical Center, Amsterdam.

### Randomization

A balanced 1:1 block (size six) randomization stratified by center will be performed directly after surgery, using Research Manager (RM; version 4.5.0.1), a web-based computer program (Fig. 1). A research nurse who is not involved in the study generates the allocation sequence with RM. Intramedullary hip nail (IMHN), dynamic hip screw (DHS) and cannulated screws are grouped for block randomization, as are total hip arthroplasty (THA) and hemiarthroplasty (HA). The intervention group ‘A’ will receive CFC therapy postoperative; the control group ‘B’ will receive standard care. Due to the nature of the study no blinding can exist as patients, family and physicians notice the use and settings of CFC therapy. Physicians randomize participants with a digital logon to the web-based system or the physician can contact the coordinating investigator and he will randomize the included participant (see Table 1 for criteria).The Informant Questionnaire for the Cognitive Decline in the Elderly (IQ-CODE) questionnaire is administered when the clinician has doubts about the cognitive state that may compromise CFC therapy sessions or study measurements (Table 1). Ideally a MMSE would be used for this purpose, however due frequently perceived pain at the accident and emergency A&E department and consequently administered narcotic analgesics, the hetero anamnestic IQ-CODE is used instead. The coordinating investigator contacts the participating hospitals on a daily basis by telephone or physically to ensure adequate and appropriate enrollment of participants and completeness of data. A list of excluded patients will be drafted.

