### Data monitoring committee

Two independent data monitors are instigated and will monitor the trial at two of the five sites where highest inclusion rates are expected. Results of the monitor will be discussed in a committee independently of the investigators and the investigators will be informed both orally and in writing. Since the overall risk of participation in the trial is considered low by the REC/IRB no external safety overseers are required by national guidelines. If selected, external auditing is possible.

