## Discussion

This multicenter study will evaluate the efficacy of intermittent application of continuous-flow cryocompression therapy administered in the first 72 postoperative hours after hip fracture surgery. Due to the multicenter design of the study the results can easily be translated to the general care of hip fracture patients. Conversely, some inequality in local hospital pain protocols is present but conversion through accepted algorithms [59, 60] make comparison feasible. Spinal anesthetized patients could have advantages over the general anesthesia group in the acute hours post-surgery in regard to pain scores and analgesic use since the effect of the latter ends immediately after surgery in contrast to the former that takes a few hours to wear off completely.

The varying types of fractures have different characteristics and demand a different surgical approach. Peritrochanteric fractures quite often have more extensive bony trauma and less soft-tissue trauma, and after surgical stabilization with a DHS or IMHN fracture micro-motion leads to prolonged and greater dynamic pain [6]. Conversely, in (hemi) arthroplasty the fracture-site is removed completely at the expense of increased (surgical-induced) soft-tissue trauma. Hence the efficacy of CFC therapy is likely to vary in patients with varying extent of soft-tissue trauma. Therefore stratification is implemented according to type of surgery that divides patients with greater surgical trauma ((hemi) arthroplasty) and lesser surgical trauma (cannulated screws, DHS, IMHN).

By nature, delirium is known to fluctuate over the day and a single DRS-R-98 measurement might not reach sufficient sensitivity for diagnosis. However with longitudinal follow-up of three times daily DOS-scores this problem is overcome for the most part. Delirium severity is assessed with more information gathered from family and personnel, over the past 24 h thereby making assessment adequate.

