### Ethics and consent to participate

Permission has been obtained from the 'Medisch Ethische Toetsingscommissie Noord-Holland' regional medical ethics committee (NL45657.094.14) and the trial is registered at www.trialregister.nl on the 23^rd^ of August 2013 with trial number: “NTR4152”. Patients with an intra or extracapsular hip fracture who meet the inclusion criteria and without apparent exclusion criteria (Table 1) are informed about the study both orally and in writing by the assessing physician e.g. the local ward doctor, staff member or consulting geriatricians. Depending on operating room capacity and patient characteristics patients will either first be transferred to the ward or will go directly to the operating room. Patients can be included pre and postoperatively within 6 h post surgery, before the first treatment starts 6 h postoperative (Fig. 1). Maximum time for consideration to participate in the study is set at 12 h. Patients approving to participate need to sign the informed consent form after which baseline characteristics are noted.

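### A single fixed block size of six per stratum, in an open-label trial, lets anyone who follows a whole stratum know up to about 22–23% of allocations in advance

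*Protocol article*

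**What the plan says.** The Randomization section fixes the scheme: "A balanced 1:1 block (size six) randomization stratified by center will be performed directly after surgery". It forms two surgery classes, since intramedullary nail, "dynamic hip screw (DHS) and cannulated screws are grouped for block randomization", and total hip and hemiarthroplasty form the other class. The Discussion confirms the second factor: "Therefore stratification is implemented according to type of surgery". No other block size is mentioned, nor any variation in size.

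On concealment and access, the article says:
- **Blinding:** "Due to the nature of the study no blinding can exist as patients, family and physicians notice the use and settings of CFC therapy".
- **Who randomises:** physicians by web logon, or "the physician can contact the coordinating investigator and he will randomize the included participant". Under Admission, it is the surgeon after the operation.
- **Overview:** the coordinating investigator contacts the hospitals daily about enrolment (Randomization) and alone holds the key-file linking patients to study numbers (Data collection and handling).
- **Timing:** "Patients can be included pre and postoperatively within 6 h post surgery" (Ethics and consent to participate).
- **Safeguards:** a research nurse outside the study generates the sequence in the web system, and a list of excluded patients is kept.

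**The concern.** Independent generation and a web system hide the list. They do not hide what can be deduced from past allocations once the block size is known. When one arm has used its three places in a block, the rest of that block is certain.

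Inclusion can still be decided after the operation, when the implant class, and so the relevant block, is settled. Some eligibility judgements leave discretion. The IQ-CODE is given only if the clinician doubts the patient's cognitive state, and postoperative haemodynamic instability is an exclusion. Someone who expects a given arm next could let that colour whether a patient is approached or included.

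The primary outcome is a pain score reported by unblinded patients. If the arms differ at entry because of selection, intention-to-treat analysis keeps that difference. The mixed model can adjust only for confounders that were measured.

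**Working it through.** **Inputs.** From Randomization: block of six, 1:1, so 3 A and 3 B; two surgery classes. Number of centres: "three middle sized teaching hospitals and one academic hospital" (Study design) gives 4, while the Data monitoring committee section would "monitor the trial at two of the five sites", which gives 5. With two classes that makes 8 or 10 strata. Total N is 160 (Sample size calculation).

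**The plan's own figure.** The article gives no figure for predictability. Its N of 160 does reproduce. With SD 2.2, difference 1.3, two-sided 5% (sidedness assumed) and 90% power, the t-based calculation gives 62 per arm, and 124 / (1 − 0.223) = 159.6, so 160.

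**Certain allocations in a complete block.** There are 20 orderings of 3 A and 3 B.
- 4th known, because the first three are the same arm: 2/20 = 0.10.
- 5th known, because the first four hold three of one arm: 8/20 = 0.40.
- 6th always known: 1.00.

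The sum is 1.5 of 6 = 25%. The closed form 2m/(m + 1) with m = 3 also gives 1.5.

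**Best guess in a complete block** (choose the arm that is behind). The success probabilities by position are 0.5, 0.6, 0.6, 0.7, 0.7 and 1.0. The sum is 4.1, and 4.1/6 = 68.3%, against 50% by chance.

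**Whole trial, with unfinished last blocks.** Simulation of 160 patients falling at random into equally likely strata:

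| Strata | Certain in advance | Share of 160 |
|---|---|---|
| 10 (5 sites × 2 classes) | 34.7 | 21.7% |
| 8 (4 hospitals × 2 classes) | 35.8 | 22.4% |
| 5 (site only, for comparison) | 37.4 | 23.4% |

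Assumed unequal strata changed the 10- and 8-stratum shares by less than 0.1 percentage point.

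**Effect of varying the block size.** The setting is exactly 16 patients per stratum (160/10) and an observer who knows which sizes are possible. Fixed blocks of six then give two full blocks plus four patients: (2 × 1.5 + 0.1)/16 = 3.1/16 = 19.4%. This is below 21.7% because every stratum stops at the same point in its third block.

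| Block sizes | Certain in advance | Best guess correct |
|---|---|---|
| 6 | 19.4% | 66% |
| 4, 6 | 6.1% | 68% |
| 4, 6, 8 | 2.2% | 67% |

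Varying the sizes removes most of the certainty and leaves the guessing almost unchanged.

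**The case against.** The strongest reply is that few people could use this. The wrap is on only during sessions, for 72 h, and only in the intervention arm; controls merely have pain scored at matching times. To predict the next allocation, one must also know who the controls were and the order of entry, within a stratum averaging 16 to 20 patients, while eight departments take part. A ward physician would usually see only part of this. That stands, and it is why the figure is an upper bound. It applies much less to the coordinating investigator.

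Some stronger readings are tempting, but the documents do not support them:
- **That a quarter of all patients, 40 of 160, are predictable.** This holds only if every block is completed.
- **That the enrolling physician is the one who randomises.** Ethics and consent to participate gives information and consent to the assessing physician, such as a ward doctor, staff member or geriatrician; Admission has the surgeon randomise. They may overlap, but the article does not say so.
- **That allocation may be released before consent.** Ethics and consent to participate puts the signed form before baseline data, and Data collection and handling puts data entry before randomisation. No further request is needed. This order does not close the gap, however, because the decision to approach a patient comes earlier still.
- **That site staff knew the block size during recruitment.** Publication in the article does not show this, and recruitment status at publication is not stated.

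The list of excluded patients gives a partial check on selective inclusion, but it does not prevent deduction.

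**Conclusion.** The point holds as a weakness in a stated design choice. Up to about 22–23% of allocations (35–37 of 160) could be known in advance. This assumes someone who knows the block size and every earlier allocation in a stratum, and strata formed by centre and surgery class. The coordinating investigator is best placed to meet the first condition.

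The harm is conditional: someone must both follow a stratum and act on it. The documents give no sign that anyone did, and no effect on the pain score can be computed from them. The case for change is that the remedy is cheap, whereas selection before randomisation cannot be repaired in the analysis.

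**What to change.** For any allocations still to be made, have the research nurse who is outside the study set randomly varying block sizes, for example 4, 6 and 8, within the same strata in the web system. Withhold the sizes from the sites and the coordinating investigator. The protocol line need only say that sizes vary and are undisclosed until recruitment ends. If recruitment has closed, nothing can be changed and the limitation should be reported.

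The cost is a software setting and an amendment under the Dissemination policy. The largest possible imbalance within a stratum rises from 3 (half of 6) to 4 (half of 8), a small price that matters mainly in small strata. The change should not be presented as a full cure, since a correct guess remains possible about two times in three.

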### Study apparatus and treatment schedule

Continuous-flow cryocompression therapy is applied by using the ‘Game Ready system’ (GRS; CoolSystems Alameda, California). Through an anatomically designed hip/groin wrap covering most of the thigh and pelvis up to the iliac crest, the GRS simultaneously delivers both adjustable continuous-flow cryotherapy and intermittent compression through a portable control unit filled with ice and water. The machine has four pressure settings: no pressure, low pressure (5–15 mm Hg), medium pressure (5–50 mm Hg) and high pressure (5–75 mm Hg). Temperature can be adjusted between 4 and 13 °C and is indicated by one, two or three snowflakes. The lowest temperature is started and maintained throughout the study if feasible. Pressure is started at ‘low’ and is increased one step per 4 treatments (Table 3). Depending on the end of surgery patients will be categorized in three treatment schedules with respective start and end-times (Table 3). If patients are uncomfortable the appropriate adjunct will be adjusted stepwise until a comfortable setting is reached, deviations are noted. Adjustments are recorded and comfortable settings are maintained according to the discomfort flowchart (Fig. 2). Patients will be treated between 10 and 12 times during the first 72 postoperative hours, each cycle lasting 30 min. Preferably, treatment cycles and control measurements during the first 72 postoperative hours are performed at fixed moments: 8:00 h, 12:00 h, 16:30 h, and 21:30 h. The GRS-wrap is only in place when CFC therapy is administered and applied/removed by the nurse.

**Table 3 Tab3:** Treatment schedule and pressure settings

End time surgery	Schedule	Start time										
10:00 – 16:00 h	*A*	16:30 h										
16:00 – 21:00 h	*B*	21:30 h										
>21:00 h	*C*	8:00 h										
Cycle no. →	1	2	3	4	5	6	7	8	9	10	11	12
OK + 0	*A:* – Low	*A* – Low										
	*B: –* Low	-										
	-	-										
OK + 1	-	*-*	*A* – Low	*A* – Low	*A* – Med	*A* – Med						
	-	*B –* Low	*B –* Low	*B –* Low	*B –* Med	-						
	*C* – Low	*C* – Low	C – Low	*C* – Low	-	-						
OK + 2					*-*	*-*	*A* – Med	*A* – Med	*A –* High	*A –* High		
					*-*	*B –* Med	*B –* Med	*B –* Med	*B* – High	-		
					*C –* Med	*C –* Med	*C –* Med	*C –* Med	-	-		
OK + 3									-	*-*	*A –* High	*A –* High
									-	*B* – High	*B* – High	*B* – High
									*C –* High	*C –* High	*C –* High	*C –* High

Regular treatment times: 8:00 h; 12:00 h; 16:30 h; 21:30 h

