### Cryocompression therapy and clinical measurements

Intervention patients start with CFC therapy 6 h postoperative, until 72 h postoperatively. A trained ward nurse will conduct the pain assessments when the patient is in bed or stationary in a chair for at least five minutes. Directly before and directly after CFC therapy vital signs including NRS-pain are measured by the ward nurse, when the patient is prone in bed for at least five minutes before commencing and five minutes after cessation of CFC therapy. In control patients only NRS-pain is measured at the same time as intervention patients would normally be assessed. All pain measurements are continued throughout the first postoperative 72 h for control and intervention patients alike (Table 4). Three times daily DOS-scores [48] will be obtained; in case of a DOS-score higher or equal to three, geriatricians diagnose and subsequently monitor delirium severity with the delirium rating scale revised 1998 (DRS-R-98) [49] on a daily basis or until the score drops below 12.25 out of 39 (Table 4). Time and amount of administered (psychotropic) medication will be documented. The nurse and ward doctor inspect the wound and dressing in accordance with routine care. Blood samples are taken at postoperative day one and three, and post-transfusion if applicable (Table 4). The timed up and go test (TUGT) is performed before discharge (Table 4). The TUGT will be administered in all patients who are able. If no weight bearing is allowed or patients are physically unable, than the test will be postponed to the outpatient visit. The mini mental state examination (MMSE) is administered for data stratification purposes [50–52], if patients are delirious during admission the MMSE is postponed to the outpatient visit.

In order to document experiences with CFC therapy all treatment patients will fill in a questionnaire at discharge, which is specifically drafted for this study (Table 5). During the study a booklet will be made available into which staff can write down prevalent occurring technical GRS-related problems.

**Table 5 Tab5:** Patient questionnaire

1. Did you feel that the pain reduced when treated with cryocompression therapy?	A	B	C	D	E
2. Would you rather have cryocompression treatment than analgesic pain treatment?	A	B	C	D	E
3. The standard setting used was the coldest; did you like this temperature setting?	A	B	C	D	E
4. Did you request the temperature setting to be upped?	Y				N

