#### De Morton Mobility Index

The DEMMI is a measure of mobility that has been validated in hip fracture patients [69-71]. The DEMMI is administered by physician or physical therapist observation of the test subject’ physical performance, measured in 15 hierarchical domains (three bed, three chair, four static balance, two walking and three dynamic balance items), each measured on a two (able/unable) or three (able/partial/unable) point scale. It takes a trained person ten minutes to administer the test in elderly patients. The raw score is converted to an interval score.

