### Complications

The surgeon monitors all complications that may occur throughout admission, in general or cryotherapy-related. After discharge the coordinating investigator verifies if all adverse events are registered and recorded on the appropriate CRF. In case of serious adverse events relating to the treatment patients will no longer receive treatment but will remain in the study for follow-up, if feasible. Severe leakage i.e. multiple bandage swaps daily is noted and registered as an adverse event. Furthermore an intragroup analysis of vital signs is made to determine possible central effects of the administered therapy. Finally, at the outpatient visit patients are assessed for adverse events that may have occurred during rehabilitation. Additional to the patient questionnaire (Table 5), intervention patients are asked about their experiences with CFC therapy. An additional insurance is taken out to financially compensate participants if applicable. Adverse events are tabulated and reported in the final manuscript.

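### The stated reason for having no blinding does not reach the assessor of TUGT, DEMMI and SPPB at 6-8 weeks, who could be kept unaware of the arm at little cost

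*Protocol article*

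**What the plan says.** The Study design section labels the trial a "prospective, open-label, parallel, multicenter, 1:1 randomized controlled, clinical superiority trial". The Randomization section then states: "Due to the nature of the study no blinding can exist as patients, family and physicians notice the use and settings of CFC therapy". No section of the article describes blinded assessment of any outcome.

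On exposure to the device, the section on the study apparatus says "The GRS-wrap is only in place when CFC therapy is administered and applied/removed by the nurse" and "Patients will be treated between 10 and 12 times during the first 72 postoperative hours, each cycle lasting 30 min". The section on clinical measurements adds: "Intervention patients start with CFC therapy 6 h postoperative, until 72 h postoperatively".

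On the mobility tests, Table 4 and the Outpatient visit section place DEMMI and SPPB only at the 6-8 week visit. TUGT is done before discharge and again at that visit. The TUGT section has a physical therapist demonstrate the test. For the DEMMI the protocol says: "The DEMMI is administered by physician or physical therapist observation of the test subject". The article names no rater for the SPPB.

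On who knows the allocation, the Randomization section has physicians, or the coordinating investigator on their behalf, randomize the patient. The Admission section gives this task to the surgeon.

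**The concern.** The protocol makes a general statement, that blinding is impossible, and supports it with a reason that covers only some of the people involved. Patients and ward nurses cannot be blinded to a wrap that the patient wears and the nurse applies. An outcome assessor who first meets the patient weeks later is in a different position.

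The sentence is a decision in the text, not a detail left to a fuller document. A full protocol consistent with it could not provide for blinded assessors.

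Functional recovery is part of hypothesis 4 in the Aim section. The DEMMI is scored by observation on able, partial or unable items, and performance tests can respond to encouragement. The Background section expects these patients to benefit most. An assessor who shares that expectation and knows the arm can create or enlarge a difference, and no later analysis could separate it from a real effect.

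**Working it through.** **1. Does the stated reason apply at 6-8 weeks?**

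- Time in the wrap: 10 to 12 sessions × 0.5 h = 5 to 6 h in total, all within the first 72 h.
- Interval to the visit: 6 to 8 weeks = 42 to 56 days. If the weeks are counted from surgery (an assumption, since the article does not say), the visit falls 42 − 3 = 39 to 56 − 3 = 53 days after therapy ended.
- Who is said to notice the therapy: patients, family and physicians. Physical therapists are not named.
- Who may rate: a physical therapist demonstrates the TUGT, and a physician or a physical therapist scores the DEMMI.

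At this visit an assessor from outside the patient's ward care has no device to see. What remains is disclosure by the patient, the file or the form, and prior involvement of the assessor. All of these can be reduced by procedure.

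**2. Does the text prevent an unblinded rater?** It does not. The Randomization and Admission sections make a physician the person who allocates, and the DEMMI section allows a physician to score. No rule keeps the two apart. The article does not say that they will be the same person, only that they may be.

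**3. Does the sample size depend on this?** It does not, and the stated figure reproduces. Inputs from the Sample size calculation section: difference 1.3, SD 2.2, alpha 5% (two-sided assumed), power 90%, dropout 22.3%.

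- Standardized difference: 1.3 / 2.2 = 0.591.
- The two-sample t-test needs 61.2, so 62 per arm and 124 in total.
- 124 / (1 − 0.223) = 159.6, so 160, as stated.

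**4. What could a rating bias do?** The documents give no size for it, so this step only illustrates a range. Assume no true effect, a shift of b SD in favour of cryocompression from rating alone, a comparison of means, and n per arm between 62 (160 × 0.777 / 2) and 80 (160 / 2). The chance of a significant result favouring cryocompression is approximately Φ(b × √(n/2) − 1.96).

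| Assumed bias b | n = 62 per arm | n = 80 per arm |
|---|---|---|
| 0 | 2.5% | 2.5% |
| 0.1 SD | 8.0% | 9.2% |
| 0.2 SD | 19.9% | 24.4% |
| 0.3 SD | 38.6% | 47.5% |

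For b = 0.2 and n = 62: 0.2 × √31 − 1.96 = 1.114 − 1.96 = −0.846, and Φ(−0.846) = 0.199.

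**The case against.** The strongest reply is that this is a declared open-label trial with a patient-reported primary outcome, and that assessor blinding on the ward would not work. Much of that stands.

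- **Delirium.** A reader might infer that delirium assessors could also be blinded cheaply, since the wrap is off between sessions. The documents do not support this. The Discussion says that severity is rated with information from family and personnel, who see the therapy. At one hospital the geriatrician takes over care except for the wound, and at another none is available daily. Vital signs are taken around sessions only in intervention patients, so ward records can reveal the arm. Hypothesis 3 concerns delirium incidence, which starts from the DOS: "Three times daily DOS-scores [48] will be obtained". DRS-R-98 follows only when the DOS reaches 3, so blinding the DRS-R-98 rater would leave this gate open.
- **Discharge TUGT.** Physical therapy runs once or twice daily from the day of surgery or the day after, inside the treatment window. A ward therapist may already know the arm.
- **Questions about the therapy.** The Complications section says that "intervention patients are asked about their experiences with CFC therapy". This follows a sentence about the outpatient visit, and a reader might infer that the arm is certain to be revealed there before function is rated. The timing is only implied: the Outpatient visit section does not list these questions, and the patient questionnaire is completed at discharge. The order of tests within a visit is also something an article may leave out.
- **TUGT is fairly objective.** It is timed, has a defined end point and averages three runs. This narrows the room for bias but does not remove it, and it does not help the DEMMI.

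None of these points reaches the 6-8 week TUGT, DEMMI and SPPB when rated by someone outside the patient's ward care.

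**Conclusion.** The point holds in a limited form. The blanket statement is broader than its reason, and the gap matters for the three mobility tests at 6-8 weeks. For these, an assessor unaware of allocation is feasible with staff the protocol already uses, and the text as it stands permits a rater who knows the arm.

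The documents do not support the wider reading that every observer-rated outcome is needlessly open. Blinding of DRS-R-98 would be partial and may need a separate rater. The DOS and the discharge TUGT are realistically open. Nor does the point bear on the primary result: NRS-pain is reported by unblinded patients whoever records it.

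The size of the bias is unknown. The percentages in the table rest on assumed biases and describe no expected effect in this trial. This is an inexpensive improvement to secondary outcomes, not a threat to the main conclusion.

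**What to change.** 1. Limit the Randomization sentence, for example: *Patients, family and treating staff cannot be blinded. Assessors of TUGT, DEMMI and SPPB at the outpatient visit are kept unaware of allocation.*
2. Have these three tests done at 6-8 weeks by a physical therapist who neither randomized nor treated the patient. Name this rater for the SPPB too. Keep allocation off the test form.
3. Do the tests before the file is opened and before any questions on complications or on experience with the therapy. Ask patients beforehand not to mention their treatment.
4. Have the assessor record a guess of the arm after the tests, so that unblinding can be reported.
5. State that DOS, DRS-R-98, the discharge TUGT and NRS-pain are assessed open, say who scores the DOS, and interpret these outcomes accordingly.

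The cost is protocol wording, form layout, visit order and some scheduling constraint at the visit. No extra staff or procedure is needed, provided each site has a therapist who was not involved in the patient's ward care. Some accidental unblinding will still occur. The sample size does not change.
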